**Fig. 1 Fig1:**
[figure not shown]
Flowchart of the study design. *After 6 months of follow-up, the control group will be provided with the same information that was given to the intervention group to raise the awareness of reducing their edible oil intake

**Fig. 2 Fig2:**
[figure not shown]
Standard Protocol Items: Recommendations for Interventional Trials (SPIRIT) Schedule of enrolment, assessment and interventions

### Study hypothesis

The knowledge of participants who receive health education regarding edible oils through WeChat will increase and they will be more willing to decrease their use of edible oils and change their unhealthy cooking and eating behaviour compared with those who have not received the intervention.

### Sample size calculation and participants

Previous studies have indicated that the daily per-capita excessive edible-oil intake (the standard value is 25–30 g/day) in households is 79.6% [26]. We set *p* = 0.8, *q* = 1 − *p* = 1–0.8 = 0.2, margin of error *d* = 0.1, *p* = 0.08, *α* = 0.05 and *Z*_*α*2_= 1.96. The sampling size is *N*= $$ \frac{{Z_{\alpha /2}}^2\times pq}{d^2} $$ =1.96^2^ × 0.8 × 0.2/0.08^2^ = 96.04 families, and considering that the sample population in this item is female, then *N* ≈ 200. The participants’ non-response rate is 10%, and the questionnaire’s qualified rate is 90%; thus, the total required sample size is *N* ≈ 250. Finally, to obtain more comprehensive cross-sectional data, we expand the sample size by three times and recruit *N* = 3 × 250 ≈ 800 participants for the status survey.

During the intervention stage, we will select 200 participants to participate in a baseline survey from the status survey, which is based on their age and education to ensure that the demographic characteristics will have no significant difference. Subsequently, they will be divided randomly into an intervention group (group A) and a control group (group B) to conduct the intervention.

### Participants and recruitment

Participants will be recruited from the following four areas (rural and urban) in Chongqing, China: Yuzhong District, Shapingba District, Dianjiang District and Wulong District. Each district represents a different level of economic development.

A publicity group will be set up during the early stage of the project. An advertisement with a short comic strip will be designed to present the study, and printed posters and leaflets will be disseminated in the cooperating communities. Women who are interested can register at the community centre. Community leaders can, if they find it appropriate, inform them about the possibility of participating in the study. Recruitment will also be done through announcements on microblogs and WeChat. Women who wish to participate will have to provide their informed consent and enrol on the study’s homepage if they meet the inclusion criteria.

The inclusion criteria are as follows: women who are between the ages of 25 and 45 years, involved mainly in housework (particularly cooking) and active daily users of WeChat (i.e. using WeChat more than three times daily).

The exclusion criteria are as follows: individuals who have never cooked, have been involved in other edible-oil experiments and those with cognitive or verbal impairments or diseases that require them to follow strict diets.

### Theoretical models

We adopt the knowledge, attitude and practice (KAP), social cognitive and stages of change (SOC) theories as theoretical models. These models are frequently used to help change health-related behaviours, such as tobacco cessation, prevention of chronic diseases and nutritional education [27–29]. A health education intervention regarding edible oils will be conducted through the WeChat platform, such that housewives can gain correct knowledge about edible oils, establish a healthy model and promote a healthy lifestyle. The status, baseline and knowledge and attitude questionnaires are designed based on KAP theory. During the intervention phase, we will provide different forms of effective intervention strategies at various stages of behavioural change based on social cognitive and SOC theories.

### K A P

This theory is one of the models used to change health-related behaviour. Knowledge (knowledge and learning) is the foundation, belief (belief and attitude) is the driving force and behaviour is the goal. Therefore, the target will produce corresponding beliefs and eventually change subjects’ behaviour after gaining health-related knowledge [30, 31]. Nutritional education is an important external condition for promoting the transformation of knowledge into behaviour.

### Social cognitive theory

Social cognitive theory is used to explain the social learning process [32, 33]. It focusses on cognitive factors, such as human beliefs, memories, expectations, motivations and self-enhancement. Social cognitive theory addresses the interactions among person, environment and behaviour. On the personal domain, the comic strip used in the intervention will provide participants with knowledge and skills regarding edible oils and cooking. Then, through observational learning, edible-oil consumption habits may improve during mealtime situations. Such improvement may increase self-efficacy and enhance behavioural capability with regard to cooking and edible-oil choices.

### SOC theory

The SOC theoretical model was proposed in 1982 by Prochaska and Di-Climente for their smoking cessation programme [34]. The theoretical basis of this model is that people’s behavioural change is a process, and each person who undergoes behavioural changes has varying needs and motivations.

This theory divides people’s behavioural changes into six stages: (1) precontemplation, (2) contemplation, (3) preparation, (4) action, (5) maintenance and (6) termination. The pace at which people move between the six stages varies, and different individuals should adopt varying cognitive and behavioural strategies to change their behaviour [35].Precontemplation: during this stage, people may be unaware of the dangers of excessive edible-oil consumptionContemplation: during this stage, people already intend to reduce their edible-oil intake, but have not yet startedPreparation: during this stage, people may have attempted to reduce their edible-oil intake and know about the benefits of reducing their edible-oil use, but do not know how to do itAction: during this stage, the daily intake of edible oils can be controlled but only for less than 6 monthsMaintenance: during this stage, the intake of edible oils has been successfully reduced for more than 6 monthsTermination: during this stage, thorough control of edible-oil intake is achieved

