### Study procedure

This study uses a combination of primary and secondary data. The quantitative cross-sectional studies will last for 4 weeks and will use WeChat as an intervention tool. A total of 800 housewives between the ages of 25 to 45 years will be recruited from different communities in Chongqing, China. A status survey will be conducted from September 2019 to November 2019. A previous study [36] has proven that age and education are associated with edible-oil intake behaviour. To eliminate the influence of confounding factors, 200 housewives with similar ages and educational levels will be selected to participate in a baseline survey. Subsequently, they will be divided randomly following a 1:1 ratio into an intervention group (group A) and a control group (group B) using computerised simple randomisation in SPSS. In the next 4 weeks, group A will receive health education through WeChat every 2 days, whereas group B will receive nothing. Each participant will then be given knowledge, attitude and behaviour tests immediately (immediate effect), 3 months (short-term effect) and 6 months (long-term effect) after the intervention. In accordance with the SOC model [35], the entire process of changing edible-oil intake behaviour among the housewives will be divided into six stages (Table 1). In addition, the changes in their behaviour stages and influencing factors will be analysed to evaluate the effects of the intervention on edible-oil intake. All subjects will read and sign a written informed consent form before their voluntary participation.

**Table 1 Tab1:** Description of intervention methods corresponding to different stages

Stages	Intervention focus
Precontemplation	Spread the knowledge and benefits related to healthy oils
Contemplation	Encourage them to start trying to control oil intake
Preparation	Guide participants on how to use edible oils in a healthy manner
Action	Help participants identify factors that affect their persistence in decreasing oil intake
Maintenance	Self-motivation
Termination	\

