### Health education intervention

Group A will receive health education through WeChat at 8.00 p.m. every 2 days. A previous study [37] has proven that WeChat push frequency has an impact on information dissemination. When the WeChat platform is used to provide education regarding edible oils, attention should be given to the time and frequency of intervention to avoid inciting negative behaviour among the participants. Thus, we will provide intervention every 2 days. Previous studies [38] have confirmed that the rate of reading articles published on WeChat accounts peaks at 9.00 p.m., and thus, we will publish the content at 8.00 p.m. to allow subjects to better accept the intervention and help us improve its effectiveness. Moreover, we will collect weekly feedback from the participants using two self-designed questions through WeChat: ‘Are you interested in the contents this week?’ and ‘What do you suggest for next issue’s content?’ The feedback will help us assess the satisfaction of the participants, and consequently, improve the contents and methods of intervention.

In accordance with the Chinese Dietary Guidelines [10] and the Chinese Dietary Reference Intakes, health education can be provided through lively presentations with text, images, videos and audios. The WeChat public platform will be used as the communication tool of the intervention group for 4 weeks. Content will include information regarding the negative effects of excessive edible-oil intake, facts about edible oils, suggested reasonable amounts of edible-oil intake and lectures on healthy oil use guidelines provided by nutrition experts. Information about the differences between saturated and unsaturated edible oils (Table 2) and their composition and nutritional properties will be provided to aid in edible-oil selection according to individual needs. Questions for increasing public interaction will also be included, such as ‘Did you control your oil intake today?’ and ‘Do you pay attention to your edible-oil intake?’ An interactive platform will be set up to allow nutrition experts to answer participants’ questions in real time. The process will last for 4 weeks, and the intervention effects on edible-oil usage will be evaluated immediately, 3 months and 6 months after intervention.

**Table 2 Tab2:** Fatty acid composition of common edible oils (%)

	Saturated fatty acid	Monounsaturated fatty acids (ω-9)	Polyunsaturated fatty acids		Trans fat

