This study aims to encourage participants to decrease their use of edible oils and change their unhealthy behaviour. We hypothesise that group A will have higher awareness and willingness to decrease their use of edible oils than group B, which will indicate that the intervention based on social cognitive theory is effective. Moreover, the knowledge and attitude of participants will improve immediately after the intervention but will decrease considerably after 6 months. Such results would imply that the immediate effect of the intervention would provide the best results, whereas the long-term effect would be poor. Moreover, we believe that the intervention results may be affected by the duration of the intervention, as confirmed in previous studies [41]. A short intervention may show that the effect is inevident. In such a case, we can appropriately increase the duration of intervention in the follow-up study. Moreover, the traditional ideas of the participants are ingrained; even if they know that the excessive consumption of saturated edible oils are among the risk factors of chronic diseases, they will still not reduce their intake. A previous study [42] has confirmed that an increase in health knowledge is not always accompanied by changes in unhealthy behaviour and the transition from the intention stage to the action stage will take time. We speculate that this condition may also affect the outcome of our intervention. In addition, we speculate that the participants’ habits and economic status may also influence their edible-oil intake behaviour.

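### Precontemplation and preparation are defined partly by what a woman knows, so the behaviour stages have gaps and overlaps, and teaching given only to group A can look like stage progress

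*Protocol article*

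**What the plan says.** All references are to the protocol article.

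- **Use of the stages (Study procedure).** The article states that "the changes in their behaviour stages and influencing factors will be analysed to evaluate the effects of the intervention on edible-oil intake". Stage change is therefore an outcome as well as a guide to content.
- **Precontemplation (SOC theory).** The description is that "people may be unaware of the dangers of excessive edible-oil" consumption. Intention is not mentioned.
- **Contemplation (SOC theory).** The woman intends to cut down and has not begun. This is intention plus non-action, with no knowledge criterion.
- **Preparation (SOC theory).** Here "people may have attempted to reduce their edible-oil intake", and they "know about the benefits of reducing their edible-oil use, but do not know how to do" it. This is an optional attempt plus two knowledge conditions.
- **Action and maintenance (SOC theory).** Both rest on controlled or reduced intake, for under or over 6 months. Termination is thorough control, with no duration given.
- **Exposure by arm (Study procedure).** During the 4 weeks, "group A will receive health education through WeChat every 2 days, whereas group B will receive nothing". Study design says that the control group gets the material after the 6-month follow-up.
- **What is taught (Health education intervention).** "Content will include information regarding the negative effects of excessive edible-oil intake", together with suggested amounts and expert lectures on healthy use. Table 1 pairs knowledge with precontemplation and how-to guidance with preparation.

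**The concern.** An ordered stage scale can measure behaviour change only if each woman has exactly one stage and moves only when her intention or behaviour moves. Here two of the three early stages depend on awareness or know-how, which is the content that group A is taught and group B is not.

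Two harms follow if a staging item is written to these definitions. Women who learn the facts without changing may be left unstaged, which loses data mainly in group A. Or whoever does the staging may place them higher, which reports a knowledge gain as progress in an analysis meant to speak to oil intake. The second error favours the intervention.

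**Working it through.** The article gives no stage distribution or staging figure to reproduce, so the check is logical. Take a woman whose intake is not controlled and cross four yes/no attributes: K (aware of dangers and benefits), H (knows how), I (intends to reduce) and A (has attempted). K treats awareness of dangers and of benefits as one attribute. Assume that an attempt implies intention. That removes 4 of the 16 combinations and leaves 12.

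Each profile was assigned twice. The **strict** reading makes each *may* in the definitions a requirement. The **lenient** reading makes the attempt optional and also lets any woman without intention stay in precontemplation.

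| K | H | I | A | Strict | Lenient |
|---|---|---|---|---|---|
| no | no | no | no | Precontemplation | Precontemplation |
| no | no | yes | no | Precontemplation and contemplation | Precontemplation and contemplation |
| no | no | yes | yes | Precontemplation | Precontemplation |
| no | yes | no | no | Precontemplation | Precontemplation |
| no | yes | yes | no | Precontemplation and contemplation | Precontemplation and contemplation |
| no | yes | yes | yes | Precontemplation | Precontemplation |
| yes | no | no | no | **None** | **Precontemplation and preparation** |
| yes | no | yes | no | Contemplation | Contemplation and preparation |
| yes | no | yes | yes | Preparation | Preparation |
| yes | yes | no | no | **None** | Precontemplation |
| yes | yes | yes | no | Contemplation | Contemplation |
| yes | yes | yes | yes | **None** | **None** |

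Counts:

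- Strict: 3 profiles with no stage, 2 with two stages, 7 with exactly one (3 + 2 + 7 = 12).
- Lenient: 1 with no stage, 4 with two stages, 7 with exactly one (1 + 4 + 7 = 12).

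Three results matter.

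1. **A gap under both readings.** The woman who is aware, knows how and has tried, but has not controlled her intake, has no stage. Preparation excludes her because she knows how, contemplation because she has started, and action because intake is not controlled. All three unstaged profiles in the strict column are aware women.
2. **A gap or an overlap.** The aware woman with no intention who does not know how has no stage on the strict reading. On the lenient reading she fits precontemplation and preparation equally.
3. **Knowledge alone can move a woman.** Compare the first and seventh rows, which differ only in K. On the lenient reading she goes from precontemplation to a choice that includes preparation, with intention, attempts and intake unchanged.

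Contemplation itself contains no knowledge criterion. The overlaps that involve it come from the knowledge wording of its neighbours.

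The link to arm comes from the design. The attributes that do the damage, K and H, are what the WeChat content teaches, and only group A receives it before the last follow-up.

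**The case against.** **The definitions are descriptions.** They sit among the theoretical models and are hedged with *may*, and no staging item is shown; a full protocol may contain one. This has some force: on the lenient reading the aware, knowing woman without intention returns to precontemplation. But the not-knowing-how condition in preparation is not hedged, so the first gap remains, and the overlap between precontemplation and preparation appears only because of the lenient reading. The point concerns definitions that are stated, not an instrument that is absent.

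**Stage is not the main behaviour measure.** This stands. The Edible-oil intake behaviour test weighs household oil over 3 days and does not depend on these definitions. Knowledge gained without behaviour change would show there as unchanged intake. This limits the damage to the stage analysis.

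**Controls may learn too.** Strengths and weaknesses concedes that the control group may obtain the information elsewhere. That would shrink the imbalance between arms, but the planned delivery is still to group A only.

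Three stronger readings are tempting and are not supported.

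- A reader might infer that all the early stages are defined by knowledge rather than intention or action. Contemplation rests purely on intention and non-action, and preparation mentions an attempt.
- A reader might infer that the Discussion predicts women who know the risk and have no intention to change. It says that "they will still not reduce their intake", which concerns intake, and it goes on to say that moving from intention to action takes time. A woman who intends but has not begun fits contemplation.
- A reader might try to put a false-positive rate on the problem. Assume 100 women per arm, 30–50% in precontemplation, 30–50% of those in group A and 10% in group B learning the dangers without any change in intention, and each scored one stage up. Spurious progress is then 0.3 × 0.3 = 9% to 0.5 × 0.5 = 25% in A, and 0.3 × 0.1 = 3% to 0.5 × 0.1 = 5% in B. An exact calculation with a pooled z-test at two-sided 5% gives a significant arm difference in 43% (9% v 3%) to 99% (25% v 5%) of trials. With 30% learning in A and 20% in B, the rates are 9% v 6% or 15% v 10%, and the result falls to 13–19%. Every input is invented. Moreover, one stage up from precontemplation is contemplation, which requires an intention that these women lack by assumption. The figures do not measure this defect.

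**Conclusion.** The concern holds for precontemplation and preparation. As worded, the stages are neither exhaustive nor mutually exclusive, and this survives both readings of the hedged terms. Because the classifying content is taught only to group A during the trial, misclassification would arise mainly there and can make a knowledge gain look like progress in the stage analysis. That arm imbalance is an inference from the design, and it assumes that staging follows the printed definitions.

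No numerical size can be given: the article reports neither how women are spread over the stages nor how many would learn without changing. The weighed oil intake is unaffected. The change should be made, but the trial's behaviour evidence does not depend on it.

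**What to change.** In SOC theory, define the three early stages by current intention and behaviour only:

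- **Precontemplation:** no current intention to reduce, whatever she knows or has tried before.
- **Contemplation:** currently intends to reduce and has not started.
- **Preparation:** currently intends to reduce and has attempted, but intake is not yet controlled, whether or not she knows how.

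Leave action, maintenance and termination as they are. Score awareness of dangers and know-how only in the 30-item knowledge and attitude questionnaire.

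With this wording all 16 combinations of K, H, I and A with uncontrolled intake receive exactly one stage, including the woman who tried, gave up and no longer intends to reduce (precontemplation). A change in K or H alone moves nobody.

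The cost is rewording three definitions before a staging item is settled. The Abstract says that the study is still in the design stage, and no visits, staff or participants are added. The small downside is that fewer women in group A may appear to progress, so the stage result may look less favourable.

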### Study procedure

This study uses a combination of primary and secondary data. The quantitative cross-sectional studies will last for 4 weeks and will use WeChat as an intervention tool. A total of 800 housewives between the ages of 25 to 45 years will be recruited from different communities in Chongqing, China. A status survey will be conducted from September 2019 to November 2019. A previous study [36] has proven that age and education are associated with edible-oil intake behaviour. To eliminate the influence of confounding factors, 200 housewives with similar ages and educational levels will be selected to participate in a baseline survey. Subsequently, they will be divided randomly following a 1:1 ratio into an intervention group (group A) and a control group (group B) using computerised simple randomisation in SPSS. In the next 4 weeks, group A will receive health education through WeChat every 2 days, whereas group B will receive nothing. Each participant will then be given knowledge, attitude and behaviour tests immediately (immediate effect), 3 months (short-term effect) and 6 months (long-term effect) after the intervention. In accordance with the SOC model [35], the entire process of changing edible-oil intake behaviour among the housewives will be divided into six stages (Table 1). In addition, the changes in their behaviour stages and influencing factors will be analysed to evaluate the effects of the intervention on edible-oil intake. All subjects will read and sign a written informed consent form before their voluntary participation.

**Table 1 Tab1:** Description of intervention methods corresponding to different stages

Stages	Intervention focus
Precontemplation	Spread the knowledge and benefits related to healthy oils
Contemplation	Encourage them to start trying to control oil intake
Preparation	Guide participants on how to use edible oils in a healthy manner
Action	Help participants identify factors that affect their persistence in decreasing oil intake
Maintenance	Self-motivation
Termination	\

